### Rigor, Reproducibility and data management

3.19

To ensure high quality data collection, written standard operating procedures will be created by the principal investigator (SD) and co-investigators (MC and KS) and disseminated to the study team members. When possible, validated questionnaires and measures were chosen. All data will be managed and stored in Research Electronic Data Capture (REDCap).

### Data and safety Monitoring

3.20

Safety data including adverse events or serious adverse events will be collected through the Pediatric Module of the Patient-Reported Outcomes version of the Common Terminology Criteria for Adverse Events (Ped-PRO-CTCAE). The Ped-PRO-CTCAE will be used to monitor adverse events in both groups at baseline, 4, 8, 12 and 16-week follow-ups. The NIH NCI Ped-PRO-CTCAE form Builder to build a study-specific custom form related to the behavioral PA intervention to provide a more specific scope of the safety of the intervention. The form has been developed in collaboration with and reviewed by pediatric oncologists. The recall period for the Ped-PRO-CTCAE is the past 7 days. The Ped-PRO-CTCAE responses are scored from 0 to 4. Adverse events reported during the study procedure that are different from those assessed at baseline will be reported to the responsible IRB.

The study will be monitored by the Data and Safety Monitoring Committee (DSMC) and will require a review every 6 months and an audit yearly.

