### Outcome assessments

3.9

All participants (n = 20) enrolled to participate in this study will receive baseline assessments the same day they provided assent, and their parents or legal guardians provided written informed consent. Moreover, they will receive follow-up assessments on weeks 4, 8, 12 and 16, as described in Table 1.

**Table 1 tbl1:** Outcome assessments over 16 weeks.

	Baseline	Follow-up week 1	Follow-up week 2	Follow-up week 3	Follow-up week 4	Follow-up week 5	Follow-up week 6	Follow-up week 7	Follow-up week 8	Follow-up week 9	Follow-up week 10	Follow-up week 11	Follow-up week 12	Follow-up week 13	Follow-up week 14	Follow-up week 15	Follow-up week 16
**Demographic information**	**I/C**																
**Cancer and treatment information**	**I/C**																
**Chronic pain**	**I/C**								**I/C**								**I/C**
**Pain medications**	**I/C**								**I/C**								**I/C**
**Pain medications (from medical records)**	**I/C**				**I/C**				**I/C**				**I/C**				**I/C**
**Psychosocial outcomes**	**I/C**								**I/C**								**I/C**
**PA behavior**	**I/C**	**I**	**I**	**I**	**I**	**I**	**I**	**I**	**I**	**I**	**I**	**I**	**I**	**I**	**I**	**I**	**I/C**
**Physical function**	**I/C**																**I/C**
Isometric handgrip strength	**I/C**																**I/C**
Aerobic capacity	**I/C**																**I/C**
Physical functioning	**I/C**																**I/C**

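### Serious adverse events are assigned to a patient-reported, intervention-specific form, with no systematic investigator-ascertained route described for both arms

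*Protocol article*

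**What the plan says.** Section 3.20 of the protocol article (Data and safety Monitoring) assigns safety collection to one instrument: "Safety data including adverse events or serious adverse events will be collected through the Pediatric Module of the Patient-Reported Outcomes version" of the CTCAE. It then describes that instrument in four ways:

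- Content: the NCI form builder is used to "build a study-specific custom form related to the behavioral PA intervention to provide a more specific scope of the safety of the intervention". Pediatric oncologists helped develop and review the form.
- Schedule: it is used to "monitor adverse events in both groups at baseline, 4, 8, 12 and 16-week follow-ups".
- Scale: "The Ped-PRO-CTCAE responses are scored from 0 to 4".
- Onward reporting: "Adverse events reported during the study procedure that are different from those assessed at baseline will be reported to the responsible IRB".

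The same section provides for review by the safety monitoring committee every 6 months and a yearly audit. Section 3.18 adds that drop-out and missing data will be reported and that, where an adverse event during the intervention is the reason, the event will be reported too.

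Section 3.14 describes a chart review by the principal investigator for prescription pain medication. Table 1 in section 3.9 has a row headed "Pain medications (from medical records"), marked for both arms at baseline and weeks 4, 8, 12 and 16. Table 1 has no row for safety.

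**The concern.** A symptom rating and a serious adverse event are different kinds of record. A 0 to 4 response says how a child rates something the form asks about. Whether an event was serious depends on facts such as an admission, an emergency visit, a fracture, a relapse or a death. As described, the form includes no seriousness criterion and no investigator assessment. A child who is in hospital may also be the one who does not complete it.

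The participants are less than a year past cancer therapy, may be non-ambulatory, and in one arm follow a home-based exercise programme. If serious events come to light only when someone happens to mention them, the safety committee and the planners of the next trial could read an absence of recorded events as an absence of events. What is mentioned would also depend on how often staff speak to the family, and that differs by arm.

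**Working it through.** The plan gives no figure to reproduce here. The check is to go through every place in the protocol article where a safety event could enter the data and ask three things: does it elicit events systematically, can it record a serious event that is not a rated symptom, and does it apply equally in both arms?

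| Source | Section | Systematic? | Records serious non-symptom events? | Both arms? |
|---|---|---|---|---|
| Ped-PRO-CTCAE custom form | 3.20 | Yes, baseline plus 4 follow-ups | Not as described; items not shown | Yes |
| Adverse event as reason for drop-out or missing data | 3.18 | Only once a child drops out or data are missing | Yes, for those children | Worded for events during the intervention |
| Events sent to the IRB | 3.20 | No; concerns events already reported | Possibly | Not limited to one arm |
| Safety committee review and audit | 3.20 | Reviews what it receives | Does not collect | Whole study |
| Chart review | 3.14, Table 1 | Yes, baseline plus 4 follow-ups | Described for pain medication only | Yes |
| Support calls and texts | 3.7, 3.18 | Contact is scheduled; no event enquiry stated | Possibly, informally | Intervention arm only |
| Oncologist's contraindication at any time | 3.4.2 | Discretionary | Not described as safety data | Both |

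No row meets all three conditions. The chart review comes closest: it is scheduled, it covers both arms and a pediatric oncologist carries it out. It falls short only because its described scope is medication.

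The difference in contact between arms follows from the schedule in sections 3.7 and 3.18:

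- Calls: weeks 1, 2, 3, 4, 6, 8, 12 and 16 = 8.
- Texts: weeks 5, 7, 9, 10, 11, 13, 14 and 15 = 8.
- Total in the intervention arm: 8 + 8 = 16 contacts in 16 weeks, one a week.
- Control arm: none described, beyond the assessments common to both arms.

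Spontaneous reports would therefore have 16 extra occasions to arise in one arm and none in the other. A child who is admitted, recovers, stays in the trial and completes the next form falls outside the drop-out route. Whether the admission is recorded then depends on an item on the form that is not shown, or on someone mentioning it.

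The point does not depend on the form's recall period. It concerns what the form can record, not how far back it looks.

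**The case against.** The strongest reply is that this is a condensed article. Definitions of serious events and investigator reporting usually sit in the full protocol, the IRB file or the monitoring plan, and section 3.29-type detail is not needed in print: section 3.19 already refers to written operating procedures. That would answer a mere silence. Section 3.20 is not silent: it says by what means serious adverse events are collected and names the form. If a separate procedure exists, the sentence misdescribes it and should be corrected.

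Other parts of the reply stand, and they limit what can be said:

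- A reader might infer that serious events have no way into the data at all, or that their loss is certain. The drop-out sentence and the IRB sentence are partial routes, and section 3.20 does not call the form the sole source.
- A reader might infer that the form is filled in by the child alone, covers only foreseen effects of exercise and has no free-text field. The article says only that it relates to the intervention. The items are not shown, who completes it is not stated, and parent-proxy reporting is used elsewhere in the trial (3.12).
- A reader might want a probability that an event is missed. The documents give no risk of serious events. An assumed risk would give the chance that an event occurs, not the chance that it goes unrecorded.
- A reader might blame the form for preventing a comparison of serious events between arms. With 10 children per arm, no method of ascertainment would support that comparison.
- Table 1 marks when medical-record data apply. It does not say the chart is opened on those dates, so one later extraction by period would also fit.

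**Conclusion.** The concern holds in a limited form. Section 3.20 makes a patient-reported, intervention-specific form the stated means of collecting serious adverse events. The other routes described are partial, and none is a systematic investigator ascertainment applied equally in both arms. Serious events that a symptom rating does not capture may be missed, and informal reporting would tend to find more of them in the intervention arm.

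No number of missed events can be given. The conclusion assumes that the form has no items that would catch such events and that no separate reporting procedure exists outside the article. If either assumption is wrong, the change needed is smaller, but the sentence in 3.20 still needs correcting. The feasibility and acceptability outcomes are unaffected. The change is worth making because the gap concerns safety in a vulnerable group and closing it costs little.

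**What to change.** In section 3.20:

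1. Keep the Ped-PRO-CTCAE and describe it as the source for symptoms.
2. State that serious and unexpected events are also ascertained in both arms from the medical-record extraction already marked in Table 1 for weeks 4, 8, 12 and 16, with fields for admissions, emergency visits, injuries, relapse and death.
3. Unless the form already has one, add an open question to child or parent about any other health problem, injury or hospital visit since the last form. This would also pick up care given elsewhere that the hospital's record may not show.
4. Report both sources to the safety monitoring committee by arm, so the extraction should be up to date before each review.
5. If the full protocol already has an investigator-reported procedure, refer to it here instead of duplicating it.

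The cost is a few extra fields in an existing extraction and one item on an existing form. No new visits are needed. If the extraction was meant to be done once at the end, doing it by period adds some staff time.

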### Study design

3.1

This is a single-site pilot randomized controlled trial where participants will be randomized in a 1:1 ratio to the 16-week behavioral PA intervention coupled with standard post-cancer directed treatment care, or to the standard post-cancer directed treatment care.

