#### Inclusion criteria

3.4.1

1)Male and female CCS diagnosed with any type of cancer;2)Completed all standard/planned cancer treatment and are stable at the time of enrollment;3)< 1-year post cancer therapy;4)Have chronic pain (pain will be self-reported by the participant, will have to be ≥ 1 on a scale of 10 and lasting for 3 months or longer);5)Between 10 and 17 years old at the time of enrollment;6)Who are and who are not non-ambulatory/wheelchair bound;7)Parent/legal guardian must be able to speak, read and understand the English language;8)Parent or legal guardian must be able to provide and understand informed consent;9)Participants must be able to provide and understand assent;10)Participants must be able to attend visits at Penn State Health Children's Hospital;11)Participant and parent/legal guardian must have access to a computer, smartphone or tablet.

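### Safety questions at weeks 4, 8, 12 and 16 with 7-day recall cover 28 of 112 days, and the IRB rule does not say whether worsening of a baseline symptom counts

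*Protocol article*

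**What the plan says.** Section 3.20 of the protocol article names one collection route for safety data: "Safety data including adverse events or serious adverse events will be collected through the Pediatric Module" of the PRO-CTCAE. On timing it states: "The Ped-PRO-CTCAE will be used to monitor adverse events in both groups at baseline, 4, 8, 12 and 16-week follow-ups". On recall: "The recall period for the Ped-PRO-CTCAE is the past 7 days". On scoring: "The Ped-PRO-CTCAE responses are scored from 0 to 4". The rule for passing events to the ethics board is: "Adverse events reported during the study procedure that are different from those assessed at baseline will be reported to the responsible IRB".

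Three other places bear on the point:

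- Section 3.4.1 makes pain an entry condition: "Have chronic pain (pain will be self-reported by the participant, will have to be ≥ 1 on a scale of 10", with a duration of at least 3 months.
- Table 1 (section 3.9) places the pain questionnaire and the psychosocial questionnaires at baseline, week 8 and week 16. Pain medication from medical records is taken at baseline and every 4 weeks.
- Section 3.18 adds that an adverse event behind a drop-out or missing data will be reported. Section 3.20 provides for review by a monitoring committee every 6 months.

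**The concern.** Two features of the stated plan weaken what it can say about harm.

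The first is the recall window. The form is given every 4 weeks but looks back 1 week, so 3 weeks of each interval are not asked about. The first of these gaps is the opening three weeks of a new home exercise programme. Section 3.7 has session length and frequency rise over time, so part of that progression also falls in gaps.

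The second is the word *different* in the IRB rule. It could mean a different kind of event, or it could also include a higher score on the same item. Everyone enters with chronic pain, so the choice decides whether a participant whose pain worsens is reported to the IRB. Two staff members could apply the sentence in opposite ways to the same child.

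At stake are short-lived injuries and flares in minors exercising at home, and consistent reporting of worsening in the symptom that all participants share.

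**Working it through.** The article gives no coverage figure, so there is none to reproduce. The check is a direct count.

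**Inputs**

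- Intervention length: 16 weeks (section 3.1), or 16 × 7 = 112 days.
- Follow-up safety assessments: weeks 4, 8, 12 and 16, so 4 (section 3.20).
- Recall: 7 days (section 3.20).
- Assumed: each assessment falls on the last day of its week, and the recall window ends that day.

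**Days covered**

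The windows are days 22–28, 50–56, 78–84 and 106–112.

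- Covered: 4 × 7 = 28 days; 28/112 = 25%.
- Not covered: 112 − 28 = 84 days; 84/112 = 75%.
- Gap before each window: 28 − 7 = 21 days. The first gap is days 1–21.

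**Chance that an event overlaps a window**

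Let an event last L days and start on any of days 1 to 112 with equal probability. It overlaps a 7-day window if it starts on one of the 7 window days or on one of the L − 1 days before it. For L up to 22 these sets do not overlap between windows, so

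chance = 4 × (7 + L − 1) / 112 = (L + 6) / 28.

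| Assumed duration L | Start days caught, 4 × (L + 6) | Chance |
|---|---|---|
| 1 day | 28 | 25% |
| 3 days | 36 | 32% |
| 7 days | 52 | 46% |
| 14 days | 80 | 71% |
| 21 days | 108 | 96% |
| 22 days or more | 112 | 100% |

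The durations are assumptions; the article gives none. The chances are also upper limits, because an overlapping event is recorded only if the custom form has a matching item and the child reports it. The form's items are not shown.

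**The IRB rule, read two ways**

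- *Different kind of event.* Pain present at baseline stays the same kind of event when it worsens, so it is not reportable. Section 3.4.1 puts all 20 planned participants in this position, provided that the custom form has a pain item.
- *Different score.* The 0 to 4 scale can show a rise, so worsening is reportable. Taken literally, an improvement is different too.

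The sentence compares events with events, which makes the first reading the more natural one. The text does not exclude the second.

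**The case against.** The strongest reply is that the plan sees more than this count suggests, and much of that reply stands.

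- **The rule limits what goes to the IRB, not what is collected.** This stands. A reader might infer that worsening pain escapes safety monitoring altogether. The documents do not support that: nothing removes baseline symptoms from the recorded form data. Pain is also measured by self-report and parent proxy at weeks 8 and 16 (sections 3.9 and 3.12), together with pain interference and intensity (section 3.15). These are outcome data summarised by group, however, and do not substitute for reporting an individual event.
- **25% is the chance of capture only for a one-day event.** This stands. Longer events do much better, so the loss is confined to brief ones.
- **Other routes exist.** This stands in part. Events behind a drop-out are reported (section 3.18), but that covers only those events. The monitoring committee reviews every 6 months, which is longer than the 16-week intervention, and no further route for events to reach it is described.
- **This is a condensed article.** The full protocol and the operating procedures mentioned in section 3.19 may deal with unscheduled serious events, so their absence here is not counted as a fault. The schedule, recall period and IRB rule are stated here and can be judged as stated.

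Two further inferences are tempting and should not be drawn. One is that the form cannot record seriousness. That would be a guess from the 0 to 4 scoring, since the form's items are not shown. The other is that the intervention arm's 8 calls and 8 texts bias the safety comparison between arms. Section 3.20 uses the same form and schedule in both groups, and sections 3.7 and 3.18 describe the contacts as delivery of the intervention, not as a source of adverse events.

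**Conclusion.** The concern holds in a limited form. As written, the safety form asks about 28 of 112 intervention days (25%) and about none of the first 21. Brief events are the ones at risk: between 25% and 46% of events lasting 1 to 7 days would overlap a recall window, against 96% or more of those lasting three weeks or longer. These percentages rest on assumed durations, uniformly distributed start days and assessments held on schedule.

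Separately, the IRB rule leaves open whether worsening of a baseline symptom is reportable, in a population where every participant has chronic pain at entry. This is an undefined term in a reporting rule. It is not a stated exclusion, and it does not mean that the data go uncollected.

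This is a cheap improvement worth making, not a fault that undermines the trial. Safety is not among the objectives in section 2, and lasting harm would nearly always fall within a recall window.

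**What to change.** Make two changes to section 3.20.

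1. Reword the IRB rule so that an event is reported if it is new or scored higher than that participant's own baseline, and so that any serious event is reported whatever the baseline.
2. At weeks 4, 8, 12 and 16, add to the existing form, in both arms, one question on injuries, worsened symptoms, and urgent or hospital care since the last assessment. Keep the 7-day recall for the existing items. The four questions together then cover all 112 days, including days 1–21.

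The cost is a short amendment and slightly more reports to process, some of which will reflect ordinary fluctuation in pain. The added question has a recall of about 4 weeks, so minor events will be remembered less reliably than under the 7-day items. If the full protocol already has a route for events between assessments, the second change reduces to stating that route and confirming that it applies equally to both arms.

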### Dissemination

3.21

The results generated from this study will be analyzed, reported and disseminated through peer-reviewed publications, presentations at conferences focused on the supportive care of patients in oncology, exercise-related meetings and academic conferences.

### STRENGHTS and Limitations

3.22

Findings from this study will document the acceptability and feasibility of a 16-week PA intervention coupled with standard post-cancer directed treatment care in children and adolescent survivors of childhood cancer, with chronic pain. Although our target sample size is small, pilot data from this study has the strong opportunity to demonstrate that the integrating a behavioral PA intervention into standard post-cancer directed treatment care will contribute to decreasing patient-reported chronic pain, decrease the need for pain medications, and improve functional and psychosocial outcomes in CCS.

Assuming this study is successful, our results will provide a compelling rationale to further examine the integration of behavioral PA interventions to mitigate chronic pain level from both a functional and quality of life perspective. Moreover, exploratory mechanism outcomes will have the potential to be explored, such as pain sensation, body sensation, and pain tolerance in CCS with chronic pain. The central hypothesis would be that exercise training may have the effect of decreasing pain by reframing the pain sensation and improving body sensations, along with increasing pain tolerance.

The literature is scarce regarding the potential of integrating PA into standard post-cancer directed care in CCS. It is possible that barriers such as fear of movement, which would limit the potential of promoting PA behavior changes. Future research in this area is greatly needed.

## Conclusion

4

There is limited evidence on how PA can impact patient reported chronic pain, need for pain medications, physical function and psychosocial outcomes in young survivors of childhood cancer. Given the great morbidity associated with the late effects of cancer therapy, the proposed study will provide essential information to guide PA recommendations for CCS with chronic pain and could inform the development of clinical care guidelines and policy making decisions for the multidisciplinary management of chronic pain in CCS.

Children and adolescents diagnosed with cancer are rare overall and the design of exercise oncology clinical trials in this population is practically challenging. A strength of our study is the inclusion of CCS diagnosed with any cancer type, though we won't have enough statistical power to perform subgroup analysis, as its a pilot study. Our pilot randomized controlled trial will help us gather data to progress toward a fully powered efficacy trial where specific cancer subtypes could be studied, assuming that the results from this current study justify doing so. Our long-term goal is to identify CCS with chronic pain that could benefit the most from our behavioral PA intervention. At this stage, we can only hypothesize that integration of a behavioral PA intervention will be an effective strategy to mitigate pain while simultaneously reducing the use of pain medications.

In recognition of the urgent need to improve the management of chronic pain, the NIH recently issued a call for projects and announced increased funding for pain research and its “Helping to End Addiction Long-term (HEAL)" initiative to speed scientific solutions to the national opioid public health crisis. Our study is in line with the research funding plan from the NIH and places us at a unique vantage point to build an outstanding and successful research project that answers the NIH call and improves supportive care for CCS.
